## Abstract

**Background:** Mental health problems are highly frequent, as well as being associated with enormous societal and economic costs and significant disability-adjusted life years. Children of parents with a mental illness (COPMI) are at a tremendously increased risk to develop disorders themselves. According to the literature, parental mental disorders launch a wave of risk factors that in turn predict the emergence of psychological problems in the offspring, and effective treatment of the parental disorder has been associated with reduced child psychopathology (launch and grow assumption). Furthermore, studies focusing on parent-child interaction demonstrate generally poorer parenting skills in parents with mental disorders, and the enhancement of such skills has been a significant mediator in improving child outcomes (parenting assumption).

**Objective:** To implement a preventive intervention for COPMI with the aim of interrupting the transmission of mental disorders in children of a parent with mental disorders. An RCT will compare state-of-the-art cognitive behavioral therapy (CBT) for a parent with mental disorders to CBT plus the Positive Parenting Program (Triple-P), a well-established and evidence-based program that enhances parenting skills.

**Methods:** A total of 634 patients seeking treatment in 8 outpatient clinics in Germany and their children will be included between January 2018 and April 2021 in the study. We use (clinical) interviews and self- as well as other-report questionnaires to assess the families at four main measurement points [T1: beginning of waiting period for psychotherapy treatment (duration of waiting period depends on usual waiting period in the study center: multiple baselines), T2: begin of parental psychotherapy, T3: post-assessment, T4: 6 months follow-up]. The total observation period will be 39 months. The patients will be randomly assigned to either the control condition (25 to 45 CBT sessions) or the experimental condition (25 to 45 CBT sessions + 10 Triple-P sessions). For evaluating the treatment process, the patients and clinicians will also be assessed after each treatment session. Furthermore, there will be a continuous assessment and report of adverse events during treatment.

**Discussion:** This trial will be the first ever to address the launch and grow as well as the parenting assumption in one study and to establish effects of the two different interventions on children's health. Our study will also likely be the first one to provide data on the comparative cost-effectiveness and will therefore provide essential information relevant for the potential implementation of such programs. The structure of the RCT will allow us to establish effects of the parental disorder(s) with/without comorbidities on children's health, to test assumptions of the trans-generational transmission model of mental disorders and bi-directional influences of different treatments on the model and to analyze specific transmission mechanisms. A deeper understanding of risk mechanisms will reveal specific transmission profiles that will result in the early detection of and effective reduction in risk factors and thus improve the health of the children at risk.

**Ethics:** The study is carried out according to the Good Clinical Practice (GCP) guidelines, the Declaration of Helsinki and its later supplements and local legal requirements. The lead ethics committee at the department of psychology at Philipps-University Marburg approved the study procedure and all study documents. A positive ethics committee vote is required at a study site, before the inclusion of a first patient at the respective site.

**Dissemination:** Via peer-reviewed publications in scientific journals, the results of this study will be made available to the scientific community. Using PsychData all primary data will be made available for re- and meta-analyses. Politicians, public health services, and stakeholders will be informed throughout the study and beyond, thus, improving public policy and health care decisions concerning preventive interventions and treatments for COPMI.

**Trial Registration:** DRKS-ID: DRKS00013516 (German Clinical Trials Register, https://www.drks.de/drks_web/navigate.do?navigationId=trial.HTML&TRIAL_ID=DRKS00013516)

## Introduction

Children of mentally ill parents (COPMI) are at a high risk of developing severe mental illness (SMI) themselves and are likely to be the next generation of mentally ill patients (1). There are studies pointing to the fact, that the parental mental disorder launches a wave of risk factors that in turn predict the emergence of psychological problems in the offspring (2). Numerous studies have shown that a parental mental illness is a powerful risk factor for the development of a SMI in children (OR in the BELLA study of 2.4) (1, 3–8). Long-term studies were also able to show that COPMI have a higher life-time risk of developing SMI themselves (ranging from 41 to 77%) with subclinical symptoms emerging earlier and more often (5, 6). The treatment of the parental disorder has been associated with improved outcomes in COPMI (7, 9–13), although there are few studies on such effects (7, 14), and they typically target the same symptoms in the child as the parent's, while such specific transmission of disorders is not typical for COPMI (1). A recent meta-analysis (k = 9) by Cuijpers et al. (14) on the effects of psychological treatment of maternal depression on children's psychopathology resulted in an overall effect-size of g = 0.40. However, the studies included were very heterogeneous (k = 5 targeting women with post-partum depression; k = 4 targeting pregnant women or mothers of young children or mothers of children with psychological/psychiatric problems/disorders), and only 2 studies explicitly applied Cognitive Behavioral Therapy (CBT) as an intervention that resulted in an overall effect of g = 0.31 (14). An earlier meta-analysis by Siegenthaler et al. (15) on preventive interventions for children of mentally ill parents demonstrated a significant relative risk reduction of 40 % for the same disorder as the parents', and overall small effects for children's internalizing (g = −0.22) and externalizing (g = −0.16) symptoms. This analysis included interventions targeting children though and not specifically those that assessed parental psychotherapy effects on their children (15). Our own meta-analysis on preventive interventions for COPMI (16) resulted in effect sizes similar to those of Cuijpers et al. (14) for young (up to 5 years of age) children (g = 0.31), and overall smaller effects for older children (g = 0.14) that equal those of Siegenthaler et al. (15). Different longitudinal studies on parental anxiety and depressive disorders present heterogeneous effects of parental treatment on children. A 6 year prospective longitudinal study on the effects of parental panic treatment demonstrated that parental treatment is a significant predictor of children's anxiety symptoms (d = 0.49–1.09 for different parental psychopathology predictors) (7). The Sequenced Treatment Alternatives to Relieve Depression (STAR^*^D) Child study was designed to examine the relation between maternal remission from depression and children's functioning and psychopathology. The study demonstrated differential effects on child psychopathology in early, late, and non-remitting mothers, with early remission being associated with reduced child externalizing problems (~5% of Child Behavior Checklist (CBCL) externalizing symptoms explained) (13); similar results have been obtained in another large longitudinal study (9).

Studies focusing on the parent-child interaction tended to demonstrate poorer parenting skills in parents with mental disorders (17–20). The enhancement of such skills has been identified as a significant mediator in improving child outcomes (21). The Positive Parenting Program (Triple P) is a well-established program to enhance parenting skills in parents of children aged 0–16 years (Triple P Kids and Triple P Teens). Universal prevention effects have been established for the Triple P Kids program (22), as well as specific effects for child psychopathology (d = 0.473) (23, 24) that differ for mothers (d = 0.61) and fathers (d = 0.42). The effectiveness of the Triple P Teen program was also shown (25). Studies explicitly testing the parenting assumption in conjunction with the launch and grow assumption are lacking so far.

Regarding psychotherapy research, there have been suggestions that moving from an approach comparing an active treatment with a control group (“does it work?”) to one that examines putatively active treatments resulting in relative questions (“which works best?” or “how do the treatments differ?”) is advisable. If demand artifacts and differentiating non-specific from specific treatment factors are included, we arrive at this formula: Treatment A = E + D_T_ + T_NS_ + T_S(A)_ and Treatment B = E + D_T_ + T_NS_ + T_S(B)_ with E = all extraneous factors; D_T_ = demand characteristics treatment; T_NS_ = non-specific treatment factors; T_S_ = characteristic-specific treatment factors. Thus, the relative difference between the two active agents in the proposed study T_S(A)_ = CBT and T_S(B)_ = CBT+PPP estimates how the two treatments differ and enables us to determine relative effects (26). Such head-to-head studies on preventive interventions for COPMI assessing differential effects have been extremely rare; the classic format are “does it work?” studies (15).

Thus, we aim to implement a preventive intervention for COPMI with the aim of interrupting the transmission of mental disorders in children of a parent with a mental disorder. The preventive intervention is planned as a two-arm RCT to establish whether strengthening parenting skills results in incremental COPMI effects above and beyond state-of-the-art CBT for parents. Including an economic evaluation alongside the clinical trial, the results of this study will have an effect on the decision making process on resource allocation for this highly vulnerable group of children of mentally ill parents.

The RCT will thus target the following hypothesis: (1) the treatment of the parental disorder will result in improved child outcome (1st arm: CBT) (2, 7, 12), and (2) the parenting skills of parents with mental illness are impaired and enhancing such skills leads to better child outcomes, thus incremental effects will become apparent in the 2nd arm: CBT+Triple P (17, 18, 20, 27, 28).

Further research questions are: Is the clinical outcome associated with reduced direct medical, direct, and indirect non-medical costs? Are CBT and CBT+PPP associated with improved quality of life for parents and children? Are CBT and CBT+PPP associated with increased psychopathology knowledge of parents and children? Is CBT+PPP associated with higher parenting skills than CBT alone? Are the effects independent of type of diagnosis, comorbid disorders, and psychopharmacology?

## Methods

### Design

The planned study is a prospective, multicenter, confirmatory, randomized controlled phase III-trial with two parallel arms comparing the effects of state of the art CBT (control intervention), and CBT + Triple P (experimental intervention) for parents with a mental illness on their children. The study is coordinated by the Department of Psychology, Clinical Child-, and Adolescent Psychology at the Philipps University Marburg (UMR).

After 3 months of study preparation (October–December 2017), a 15 months recruiting period has started in January 2018. The assessment period (first patient in until last patient out) will last for a total of 39 months. Six months are scheduled for data freeze, data cleaning and analysis. Thus, the duration of the whole trial is 48 months (see Figure 1).

**Figure 1 F1:**
[figure not shown]
Study design.

Using the same instruments (self- and other-report questionnaires as well as (clinical) interviews) each time, patients, and their families will be assessed at four main measurement points (see Figure 2): pre-assessment 1 (T1, beginning of waiting period for psychotherapy treatment (duration of waiting period depends on usual waiting period in the study center: multiple baselines), pre-assessment 2, (T2, beginning of parental psychotherapy), post-assessment (T3, after parental psychotherapy), follow-up-assessment (T4, 6 months after parental psychotherapy). Altogether, assessment time comprises between 4 and 5 h for each main assessment (T1, T2, T3, T4) for each family. Patients and therapists are also assessed after each treatment session for treatment fidelity and satisfaction. Every fifth session, the remission status of the patient is also assessed.

**Figure 2 F2:**
[figure not shown]
Study assessment points. *Waiting period can vary according to the regular waiting period in the study centers.

### Participants

A total of 634 parents with a mental illness (patients) shall be included in the study. The following criteria must be met for patients and their families to be included in the study: (1) patient seeks outpatient psychotherapeutic care, (2) patient currently meets diagnostic criteria for DSM-5 disorder (29), and (3) patient is caring for at least one child between the ages of 1.5–16 years. Patients and their families will not be included in the study if (1) patient is already in psychotherapeutic treatment, (2) patient needs acute inpatient treatment (e.g., acute risk of committing suicide or acute psychosis), (3) all children fulfill criteria for a severe mental illness and are in need of prompt treatment, (4) patient uses benzodiazepines continuously (intermittent drug use less than once every 2 weeks is allowed), or (5) family has insufficient German language skills. No further exclusion criteria will be applied. Hence, we seek to establish effects of parental psychotherapy on children in a naturalistic setting and want to specify the effects of the transgenerational transmission to test the launch and growth assumption. Patients in need of acute inpatient treatment are referred to cooperating hospitals. For children in need of prompt care, treatments are initiated at the study sites or the families are referred to other local specialists/psychiatric hospitals.

The study will be conducted at eight university outpatient clinics throughout Germany: Bielefeld, Bochum, Gießen, Landau, Leipzig, Mainz, Marburg, and Munich. All cooperating sites have established outpatient clinics for research and teaching as well as psychotherapy training institutes and are well-known specialized treatment centers for psychotherapy. The patients are primarily recruited from the university outpatient clinics at each study site. The study centers have continuous experience in conducting psychotherapy studies with recruitment of large patients numbers (30, 31). The patients to be recruited per center and fulfilling all inclusion criteria will be attainable over a 15-month acquisition period at all study sites without the need to change the existing infrastructure. If possible, all children between 1.5 and 16 years of age (at T1) and a partner living together with the family shall be included in the study. A legal guardian not living together with a child can upon request be offered to participate in the study and to complete questionnaires about the respective child. Inclusion only takes place if the family participates voluntarily in the study. There is no compensation for study participation.

### Interventions

All patients will receive between 25 (short-term) and 45 (long-term) weekly or bi-weekly sessions of individual state of the art Cognitive Behavioral Therapy (CBT). A high frequency therapy with more than one session per week is also allowed. Depending on the amount and the frequency of therapy sessions, the treatment will usually last between 6 and 12 months. The number of sessions and therapy duration will be documented, thus, allowing us to include therapy duration and number of sessions as a moderating factor in the analyses.

CBT can be considered the current “treatment of choice” for mental disorders in general (32). Central elements are psychoeducation that provides a framework for psychotherapy, cognitive components (i.e., debate of dysfunctional cognitions alias Beck), as well as behavioral interventions (i.e., exposure). As all study sites are outpatient clinics for research and teaching located at university psychology departments, they commit to the highest possible state of the art standard for CBT as outlined in “proceedings in psychotherapy/Fortschritte der Psychotherapie” of which [name] (Co-PI of COMPARE-family) is an editor (33). As the study shall be conducted as naturalistic as possible and a broad range of disorders shall be included, no specific study manual has been created, rather, the respective therapy manuals of the proceedings in psychotherapy will be used in this study.

Patients randomized to the experimental group will receive 8–10 additional group or individual sessions of the Positive Parenting Program (Triple P) parallel to the last third of the psychotherapy sessions to test whether the enhancement of parenting skills will result in improved child outcome, as suggested in different studies (17, 18, 20, 27, 28), above and beyond parental CBT. Triple P is a well-established, widely used and evidence-based program to enhance parenting skills. The Triple P Kids program can be used in groups or individual sessions with parents of children aged 0–12 years (34, 35) and the Triple P Teens program in groups with parents of children aged 12–16 years (36). The Triple P elements are: (1) promotion of a positive parenting style, (2) promotion of child development, (3) dealing with problem behavior, (4) behavior training sessions (34–36).

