### Pre-assessment T1 and Assessment of Eligibility

After an initial screening of eligibility for an as early and effective as possible selection of patients and their families and a regular intake consultation with the patient in the outpatient clinic, the patients and their families (children over the age of 6 years) are invited to an informational session at the study center. During this session, the families are informed about the study procedure before signing their consent to participate in the study. For pseudonymized data collection, each participant is assigned a Screening-ID. To assess a broad range of DSM-5 based psychological disorders and comorbid ones as well as severity ratings, structured clinical interviews for patients (DIPS), and children (Kinder-DIPS parent version or SIVA) are conducted with the patient respectively a parent (for each child separately). The parent, with whom the Kinder-DIPS/SIVA is conducted, has to be the same for all children of a family at all measurement points. The in- and exclusion criteria are checked on the basis of the information collected during the screening and the diagnoses based on the clinical interviews. Feedback to diagnoses is given in a separate session. If a patient and its family fulfill all the in- and none of the exclusion criteria, the family is included in the trial and records for the eCRF are created for all the included family members. The family is invited to another session in which interviews about knowledge about mental disorders are conducted with each included family member. After this session codes are handed out with which the family members can log into REDCap at home to complete the questionnaires. Forms with REDCap-codes for the children's caregivers or teachers (one caregiver/teacher for each included child) are also handed out to the family with the request to forward them to the respective caregiver/teachers. There is no reference to the clinical trial of the COMPARE-family project on the caregiver/teacher's form; rather, the questionnaire is generally presented as part of a study at the department of psychology the UMR. After the final inclusion in the study, the randomization to one of the two treatment arms (CBT or CBT+Triple P) takes place. If needed, further probatory sessions can take place at the study centers. In a separate feedback session, the patient is informed about the treatment condition and results of the diagnostic process.

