## Discussion

We expect that in arm I (CBT), the parents will improve through treatment as will their children (2, 7, 12). Since, parenting skills of parents with a mental illness are likely impaired and enhancing such skills leads to better child outcomes (17, 18, 20, 27, 28), we expect that additional incremental effects will become apparent in arm II (CBT+Triple P). We will use the Positive Parenting Program (Triple P) in addition to CBT, as Triple P is an evidence-based, widely used, and well-established program. The positive effects of Triple P have been demonstrated in parents and children (22, 23, 78), although incremental effects above and beyond parental CBT have not been researched in conjunction with COPMI so far.

The established magnitude of this specific incremental effect will result in precise recommendations for this high-risk group that will impact clinical practice (i.e., practice parameters, treatment guidelines). As outlined above, COPMI are most likely to constitute the next generation of patients with a mental illness, and we assume that this intervention will contribute to the prevention of SMI in this specific high-risk group.

As studies so far have focused primarily on specific disorders (e.g., anxiety, depression) and have excluded comorbidities (1, 3), though comorbidities actually occur with the most patients, the COMPARE study will fill this research gap by including a broad range of mental disorders and by not excluding comorbidities. A double baseline measurement with multiple baselines depending on the usual waiting periods in the study centers (T1: 1st assessment of parents and children via clinical interviews and questionnaires; T2: 2nd assessment with the same instruments) will enable us to assess parental disorder effects on the child that can then be related to parental treatment effects (T3: after completion of 25 short-term to 45 long-term sessions of state-of-the-art CBT or CBT+TripleP) for a 6-month follow-up (T4). As there are differential parental psychotherapy effects on children depending on the parental remission status (early, late, and non-remitters), we will also assess such effects (9, 13). By including different therapy durations (short- vs. long-term therapy) we will be able to shed light on treatment duration effects.

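### Delivered therapy duration and session number arise after randomisation, so their planned use as a moderating factor cannot carry the promised conclusions about duration effects

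*Protocol article*

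**What the plan says.** On the amount of therapy, the Interventions section states: "All patients will receive between 25 (short-term) and 45 (long-term) weekly or bi-weekly sessions". On its length: "Depending on the amount and the frequency of therapy sessions, the treatment will usually last between 6 and 12 months". It then says that the number of sessions and the duration will be recorded, "allowing us to include therapy duration and number of sessions as a moderating factor in the analyses". The variables meant are thus the delivered ones. The Discussion gives the intended reading: "By including different therapy durations (short- vs. long-term therapy) we will be able to shed light on treatment duration effects".

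On timing, the section on pre-assessment T1 and eligibility states: "After the final inclusion in the study, the randomization to one of the two treatment arms (CBT or CBT+Triple P) takes place". The patient then learns the arm: "In a separate feedback session, the patient is informed about the treatment condition and results of the diagnostic process". The waiting period, T2 and therapy follow.

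In the experimental arm only, Triple P is added "parallel to the last third of the psychotherapy sessions".

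The primary model in Statistical Methods adjusts for centre, comorbidities, number of children, T2 TRF score and waiting time. It contains neither sessions nor duration. Analyses beyond the primary and secondary outcomes are described there as exploratory.

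**The concern.** A moderator of a randomised comparison should be fixed before randomisation, so that the arms stay comparable at each of its levels. Delivered sessions and duration accumulate during treatment. The article does not say how a patient comes to have 25 rather than 45 sessions, and no planned therapy type is recorded before allocation.

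Two features make a problem plausible. Session number may follow prognosis or progress. The arm may also influence the course of CBT, since the patient knows the allocation and Triple P is attached to the final third of therapy in one arm.

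At stake is the statement about short- versus long-term therapy. If parents with a poorer prognosis stay longer, longer therapy will look worse for children even when length has no effect. The arm difference within levels of session number can also be distorted, under narrower conditions set out below.

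**Working it through.** **The plan's own figures.** The article gives no figure for a duration analysis. Its sample size reproduces: for d = 0.25, two-sided alpha 0.05 and power 0.80, the t-test solution is 252.1, so 253 per group and 506 in total. With 20% dropout, 253/0.8 = 316.25, so 317 per group and 634 in total. This point does not touch them.

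**Order of events.** Eligibility at T1, randomisation, patient told the arm, waiting period, T2, therapy, T3. Sessions and duration are complete only at the end of therapy, so they are post-randomisation variables.

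**What can be biased, and when.** Let A be the arm, U a latent prognosis (higher is worse), S sessions in SD units and Y the child score in SD units, with no true effect of S:

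- S = aU + cA + noise, with Var(S|A) = 1
- Y = bU + noise (a true arm effect simply adds to the coefficient of A)
- Hence E(Y|S,A) = ab·S − ab·c·A

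The spurious slope on sessions is ab, the spurious arm shift given sessions is −abc, and the spurious interaction is zero. None of a, b and c is in the documents. The only loose anchor is the Introduction's figure of about 5% of externalizing symptoms explained by early maternal remission, which gives b ≈ √0.05 = 0.22. Results for a = 0.5 and c = 0.3:

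| b | Slope ab | Share of d = 0.25 | Size of arm shift abc | Share of d |
|---|---|---|---|---|
| 0.22 | 0.11 | 45% | 0.034 | 13% |
| 0.30 | 0.15 | 60% | 0.045 | 18% |

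With a = 0, both biases are zero.

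**Interaction, by simulation.** Assumptions: 506 independent patients, 4,000 runs per scenario, true arm effect −0.25 SD for everyone, no true moderation, b = 0.5. Sessions have mean 35 and SD 5 and are limited to 25–45. The model is linear with an arm-by-sessions term.

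| Mechanism for sessions | Interaction per 10 sessions | Tests with p < 0.05 | Arm effect at 35 sessions | Arm effect, under 35 / 35 and over |
|---|---|---|---|---|
| Unrelated to prognosis | −0.01 | 5% | −0.25 | −0.24 / −0.25 |
| Unrelated, 3 more sessions in experimental arm | 0.00 | 5% | −0.25 | −0.25 / −0.25 |
| Correlation 0.5 with prognosis in both arms | 0.00 | 6% | −0.25 | −0.25 / −0.25 |
| As above, 3 more sessions in experimental arm | 0.01 | 5% | −0.40 | −0.35 / −0.34 |
| Link half as strong in experimental arm | −0.25 | 28% | −0.25 | −0.15 / −0.35 |
| Link in control arm only | −0.52 | 80% | −0.25 | −0.05 / −0.45 |

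The fourth row agrees with the formula: 0.5 × 0.5 × (3/5) = 0.15, and −0.25 − 0.15 = −0.40.

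So a false duration slope needs only that sessions depend on prognosis. A biased arm effect given sessions also needs the arm to shift sessions. A false interaction needs the prognosis link to differ by arm.

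**The case against.** The strongest reply is that little is specified. The wording about sessions is permissive, names no model, outcome or test, and does not say that the arm contrast is what would be moderated. The form of an exploratory analysis can properly be left to the full protocol or SAP. That stands as far as missing detail goes. It does not remove the point, because the article itself names delivered sessions and duration as the moderating factor and announces the conclusion to be drawn from them.

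Several stronger readings are tempting, and the documents do not support them:

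- **That session number is driven by response.** Remission status is assessed every fifth session, but nothing links it to how many sessions are given. The dependence is an inference.
- **That the moderator result would be biased.** With the same prognosis link in both arms the interaction is unbiased, even with an arm shift. The supportable word is may.
- **That Triple P lengthens CBT.** It runs alongside CBT, and the 25–45 range applies to both arms. An arm shift is possible but not documented.
- **That remission status is misused in the same way.** The Discussion says, of parental therapy effects on children "depending on the parental remission status (early, late, and non-remitters), we will also assess such effects". It does not propose remission as a moderator of the randomised comparison, and Statistical Methods lists the BSI, by which remission is assessed, among the mediators.
- **That the trial's main result is at risk.** Neither variable is in the primary model.

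**Conclusion.** The point holds in limited form. The article assigns a moderating role to two variables that arise after randomisation and promises a reading about duration effects that such an analysis cannot support on its own. The result may be biased. Whether it is, and by how much, depends on how session number is determined, which the article does not state.

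The figures above illustrate size under assumed correlations and are not estimates for this trial. With a = 0.5 and b between 0.22 and 0.30, the spurious sessions slope is 0.11–0.15 SD per SD of sessions; with c = 0.3 the conditional arm effect moves by 0.034–0.045 SD. A false interaction arises only under arm-specific links. Both primary hypotheses, their model and the sample size are unaffected.

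**What to change.** 1. Do not use delivered sessions or duration as a moderator of the randomised comparison. Report both descriptively by arm.
2. Present any analysis of duration against child outcome as an exploratory, non-causal association adjusted for baseline severity, noting that this adjustment does not remove confounding by response during therapy.
3. Reword the Discussion sentence on duration to match.
4. If a moderator is wanted, use a variable fixed before randomisation, such as the planned short- or long-term type where it was recorded by then.

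Items 1 to 3 cost only wording. Item 4 has real limits: planned type is coarser than delivered therapy and may differ from it, it may not be known at randomisation because further probatory sessions can follow, and it cannot be added for patients already randomised, recruitment having begun in January 2018.
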